### Schedule of Enrollment, Interventions, and Assessments

The participants will undergo screening and baseline assessments before randomization and electroacupuncture administration at 2 Hz or 100 Hz during visit 1. Pain NRS scores will be recorded immediately before the intervention and immediately after and at 15 minutes, 1 hour, 2 hours, 4 hours, and 24 hours after electroacupuncture. Photoplethysmography-derived PRV and radial pulse tonometry data will be recorded at baseline and after 2 hours under standardized resting conditions. The same schedule will be followed for visit 2 after the 7-day or longer washout period.

### Outcome Measures

The primary outcomes are baseline-adjusted changes in pain intensity (11-point NRS; 0-10) at 15 minutes and 2 hours after each intervention. Change scores will be calculated as the postintervention NRS score at each specified time point minus the visit-specific preintervention baseline NRS score. The 15-minute time point was selected to evaluate immediate analgesic response after the 15-minute electroacupuncture stimulation, and the 2-hour time point was selected to evaluate whether the short-term analgesic response is maintained during the standardized in-clinic observation period.

Secondary outcomes will include pain NRS scores immediately after and at 1, 4, and 24 hours after electroacupuncture; pain location and quality; Photoplethysmography-derived PRV indexes (eg, total power, low frequency, high frequency, very low frequency, and low frequency–to–high frequency ratio); radial pulse tonometry parameters (eg, stroke volume, stroke volume index, cardiac output, systemic vascular resistance index, and waveform features); and physical activity metrics (steps, distance, and energy expenditure) from a wrist-worn device during the 2-hour in-clinic observation period.

### Randomization, Allocation, and Blinding

Participants will be randomized in a 1:1 ratio to 1 of 2 treatment sequences (AB or BA) using block randomization with permuted blocks of varying sizes based on a computer-generated allocation list created by an independent statistician. To ensure allocation concealment, a study coordinator not involved in enrollment will prepare opaque, sequentially numbered, sealed envelopes containing the sequence codes and store them securely until assignment. Site investigators will enroll eligible participants. At each visit, the treating practitioner will confirm the assigned intervention immediately before treatment, and the contents of the allocation envelope will not be disclosed to participants or outcome assessors. The assigned randomization number will be recorded in the eCRF, and opened envelopes will be retained separately to maintain an audit trail. Participants will be informed that 2 electroacupuncture stimulation modes are being compared but will not be told whether 2 Hz or 100 Hz are applied at each visit. The treating practitioner cannot be blinded because the electroacupuncture device must be set to the assigned frequency. Outcome assessors collecting pain NRS scores and personnel responsible for data entry and statistical analysis will remain blinded to frequency allocation whenever feasible. Although participants will not be informed of the stimulation frequency assigned at each visit, perceived sensory characteristics, such as rhythm or pulsation, may differ between 2-Hz and 100-Hz stimulation. Therefore, some participants may infer the stimulation mode, and participant masking to stimulation frequency may be incomplete.

### Sample Size

A total of 26 evaluable participants will provide approximately 80% power (2-sided α=.05) to detect a clinically meaningful 1.0-point difference in pain NRS change scores between stimulation frequencies assuming an SD of 2.0 and a within-subject correlation of 0.6 [25-28]. To account for potential sequence imbalances and an anticipated 10% dropout rate, 30 participants will be enrolled. This sample size is planned for within-participant comparison of stimulation frequencies and is not intended to establish the effectiveness of electroacupuncture compared with no electroacupuncture.

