The analgesic effects of electroacupuncture are frequency dependent. Low-frequency stimulation (2 Hz) preferentially elicits β-endorphin and enkephalin release, whereas high-frequency stimulation (100 Hz) engages dynorphin-mediated pathways. These findings suggest that the peptide systems are partially distinct [20]. Responsiveness varies across individuals, and intrinsic factors may contribute to this heterogeneity [21]. Procedure- and patient-specific factors also influence postoperative pain intensity [9,22]. Therefore, a 2 × 2 crossover design with intraindividual comparisons is well suited to compare the effects of 2-Hz and 100-Hz stimulation and control for interindividual variability.

The primary hypothesis of this study is that 2-Hz and 100-Hz electroacupuncture will produce different short-term analgesic responses, measured as baseline-adjusted changes in pain numerical rating scale (NRS) scores at 15 minutes and 2 hours after stimulation. This frequency-masked, active-comparator, 2 × 2 randomized crossover study aims to compare relative responses to bilateral ST36 to SP9 electroacupuncture at 2 Hz and 100 Hz.

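### Two primary outcomes share one alpha and one power figure, and the article gives no success rule under which the stated 5% and 80% both apply

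*Protocol article*

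**What the plan says.** The Introduction of the protocol article states one hypothesis: "The primary hypothesis of this study is that 2-Hz and 100-Hz electroacupuncture will produce different short-term analgesic responses". It measures this at two times and does not say whether a difference at one time is enough.

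Outcome Measures makes both times primary: "The primary outcomes are baseline-adjusted changes in pain intensity (11-point NRS; 0-10) at 15 minutes and 2 hours after each intervention". Each has its own purpose. The 15-minute score addresses the immediate response, and the 2-hour score addresses whether that response lasts through the in-clinic observation period.

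Sample Size gives a single calculation, for 26 evaluable participants. Its claim is "approximately 80% power (2-sided α=.05) to detect a clinically meaningful 1.0-point difference in pain NRS change scores". The inputs are an SD of 2.0 and a correlation of 0.6 within participants. No time point is attached to the 1.0-point difference, and alpha is not divided. Enrolment is set at 30.

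Statistical Analysis describes linear mixed models for NRS change with treatment, time, period and sequence effects and the visit-specific baseline as covariate. It does not say which contrast is primary, in what order the two outcomes are tested, or how alpha is shared between them.

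**The concern.** An alpha and a power figure describe a decision rule. With two primary outcomes the rule must say whether success means a difference at either time, at both times, at one time and then the other, or on an average of the two. The article quotes .05 and about 80% beside two primary outcomes without saying which.

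The two simplest rules each break one of the figures. Under either-suffices with no adjustment, there are two chances of a false positive and the error rate exceeds 5%. Under both-required, there are two chances to miss and the power falls below 80%.

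The Discussion says that the results will inform the choice of frequency for later trials. If the two times disagree, the conclusion depends on which rule is used, and a rule chosen after seeing the results could not be defended as prespecified.

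**Working it through.** **Inputs.** From Sample Size: difference 1.0, SD 2.0, within-subject correlation 0.6, two-sided alpha .05, 26 evaluable, 30 enrolled. From Outcome Measures: two primary outcomes. The correlation r between the 15-minute and 2-hour treatment differences is not given. I assume 0.5 to 0.9 and show independence as the extreme. The power figures assume a true 1.0-point difference at both times, with the same SD.

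**1. Reproduce the stated figure.**
- SD of the within-participant difference = 2.0 × √(2 × (1 − 0.6)) = 1.789.
- n = (1.789 × (1.960 + 0.842) / 1.0)² = 25.1, rounded up to 26.
- Power at n = 26: 81.3% by the normal formula, 78.1% by the noncentral t with 24 df.

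So 26 reproduces as one paired comparison at the full .05.

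**2. Either outcome suffices, no adjustment.** Familywise error = P(|Z₁| > 1.96 or |Z₂| > 1.96) under the null, with (Z₁, Z₂) bivariate normal with correlation r. Under independence it is 1 − 0.95² = 9.75%.

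**3. Both outcomes required, each at .05.** Joint power = P(both significant) at n = 26. The noncentrality is 1.0 / (1.789 / √26) = 2.85 for each test.

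**4. One pooled contrast (mean of the two times) at .05.** SD of the pooled difference = 1.789 × √((1 + r) / 2). The power shown is t-based with 24 df.

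| r | Step 2: familywise error | Step 3: joint power, normal | Step 3: joint power, t | Step 4: pooled power, t |
|---|---|---|---|---|
| 0.5 | 9.1% | 70.6% | 66% | 88% |
| 0.7 | 8.3% | 73.0% | 69% | 84% |
| 0.9 | 7.0% | 76.5% | 73% | 80% |

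The normal column is the like-for-like comparison with the stated 80%, because the normal formula gives 26. The t column starts from 78.1%, so part of its gap comes from the t distribution and not from multiplicity.

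**5. Alpha split equally (.025 each).** Power per outcome at n = 26 is 72.9% (normal) or 67.7% (t, 24 df).

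**6. Fixed sequence.** The first outcome is tested at .05 and the second at .05 only if the first is significant. Familywise error stays at 5%. The first outcome keeps 81.3% (normal) or 78.1% (t). The chance of reaching significance on the second outcome equals the joint power in step 3.

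**7. If all 30 recruited participants are evaluable.** On the t distribution with 28 df, a single test at .05 has 84% power, a test at .025 has 75%, and both-required has 74% to 80% for r from 0.5 to 0.9.

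**The case against.** The strongest reply is that the article does not say the two outcomes are tested separately. There is one primary hypothesis, and the model as listed has a treatment effect and a time effect but no treatment-by-time term. If it is fitted to the two primary time points, it gives one treatment effect and one test at .05, with power of about 80% to 88% (step 4). Outcome Measures also hints at an order, immediate and then maintained, and a fixed sequence would keep 5% and about 80% for the first outcome. A reader might therefore infer from the either/both comparison that the stated alpha and power are wrong under every reading. The document does not support that: these two rules preserve them.

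This reply limits the point but does not remove it. The article does not call the pooled effect primary, does not say which of the postintervention times enter the model, and gives each primary time its own question, which an average would not answer. It states no testing order either.

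A second reply is that multiplicity rules commonly sit in an analysis plan, which is not shown here. That is fair, and the absence of such a rule from a condensed article is not the finding. The finding is the power statement as published: one unnamed comparison beside two primary outcomes. Even if an unseen plan fixes a sequence, the 80% belongs to the first-tested outcome only, and the Sample Size section does not say so.

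A third reply is that the trial also aims to estimate effect size and variability for later trials, and that statistical personnel are to remain blinded whenever feasible until the data are final. Both lower the stakes. The document nevertheless states a primary hypothesis, a two-sided alpha, a power and a difference it calls clinically meaningful.

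**Conclusion.** The point holds as a mismatch between the primary outcomes and the power statement. The 26 participants and about 80% power fit a single paired comparison at .05, and the article does not say which comparison that is. Under unadjusted either-suffices testing, the error rate would be about 7.0% to 9.1% instead of 5%. Under both-required testing, power would be about 71% to 77% (normal) or 66% to 73% (t) instead of about 80%. Under a fixed sequence (first outcome only) or one pooled contrast, the stated pair holds, but neither is stated.

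These ranges rest on the assumed correlation of 0.5 to 0.9 and, for power, on a 1.0-point effect at both times. The shortfall is moderate and shrinks if all 30 participants are evaluable. It should be fixed before analysis, but it does not undermine the trial. The article also does not support a prediction that a result at one time would be reported as confirming the hypothesis; it leaves that open.

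**What to change.** Before database finalization and unblinding, prespecify one rule in the analysis plan:

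- **Fixed sequence (preferred).** Test 15 minutes at two-sided .05, and test 2 hours at .05 only if the first is significant. This follows the document's own order of an immediate and then a maintained response. Cost: the 2-hour claim becomes conditional on the first.
- **Holm**, if no order is wanted. Cost: power per outcome may fall to as low as about 68% (t) to 73% (normal) at n = 26.
- **One named pooled contrast** over the two times. Cost: the separate 15-minute and 2-hour results become supportive.

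Then amend the Sample Size section to say that the roughly 80% applies to the first-tested outcome or the named contrast only. With a fixed sequence or Holm, also give the power for the remaining outcome.

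The cost is a short addition to the analysis plan and a clarification of the sample-size paragraph, with no extra participants. All 30 have been recruited, and formal analysis is planned only after database finalization in late 2026, so settling the rule is more practical than enlarging the trial.

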### Recruitment Strategy

To recruit participants, promotional posters or informational materials will be displayed within the conducting institution. If participant enrollment is delayed during the clinical trial, local advertisements, such as in subways, buses, and apartment bulletin boards, may be implemented, and online advertisements may also be used.

### Statistical Analysis

The primary analysis will be conducted according to the intention-to-treat principle. A per-protocol analysis will be performed as a sensitivity analysis. Linear mixed models with the participant as a random effect will be used to determine the effects of treatment (2 Hz vs 100 Hz), time, period, and sequence on the changes in NRS scores from baseline. To account for baseline differences, the visit-specific baseline NRS score will be included as a covariate in the linear mixed models, and days since surgery will be treated as an additional covariate or sensitivity analysis variable. Age will be summarized as a baseline characteristic, considered as a covariate in exploratory sensitivity analyses if performed, and interpreted as hypothesis generating because the study is not powered for subgroup comparisons. Intravisit pretest-posttest comparisons may be performed using paired tests for descriptive support. Missing data will be handled using mixed models without imputation. However, they will be imputed using multiple imputation for sensitivity analyses. Statistical analyses will be performed using R (version 4.5.0 or later; R Foundation for Statistical Computing).

### Data Collection and Management

Data will be recorded in a validated eCRF. The date and type of index surgery, postoperative day at screening, postoperative day at each intervention visit, visit-specific baseline NRS score, concomitant analgesic use, and any deviations from standardized measurement procedures will be recorded. Quality control, audit trails, query handling, and backups will be conducted in accordance with institutional standard operating procedures. Access will be role based, and identifiable information will be stored separately from the analytical datasets.

### AE Monitoring and Management

AEs, defined as any harmful or unintended symptoms or abnormalities, will be recorded from informed consent to the end of follow-up. For each AE, the event type, onset date, severity, and outcome or resolution will be documented, and any serious AEs will be reported to the institutional review board (IRB) and relevant authorities according to institutional policy. All AEs will be managed using standard medical procedures and routine clinical protocols to ensure participant safety throughout the study.

### Informed Consent and Consent Acquisition

The researcher will explain the purpose, methods, risks, and participant protections of the study before any clinical procedures. The participants will provide voluntary consent to take part and sign an informed consent form. They will be provided with a copy of the form, and the institution will retain the original. Separate consent will be obtained for data sharing with third parties, secondary research use, and the collection and use of personal data.

### Ethical Considerations

This study protocol (ICT_25_3-2; version 1.1) was approved by the IRB of Catholic Kwandong University International St. Mary’s Hospital on August 27, 2025 (approval 25-IRB-050-1). Any modifications to the protocol will require a formal amendment, which must be reviewed and approved by the IRB before implementation.

### Data Monitoring

Designated monitors will conduct regular on-site visits (once for every 5 participants enrolled) and maintain telephone contact with the study site as needed. During visits, monitors will primarily review source documents, study intervention and device accountability logs, and essential research files while also assessing overall trial progress and promptly discussing any issues with the investigator if problems arise. Access to medical records will be limited to what is necessary, and confidentiality will be protected via password-restricted eCRFs and worksheets. Given the low anticipated risk of the intervention and the absence of a planned interim analysis, a data monitoring committee will not be convened.

## Results

The study was funded in January 2025. Participant recruitment began in September 2025. As of June 8, 2026, 30 participants had been recruited. Data collection is expected to be completed by August 2026, and formal outcome analyses are planned to begin after completion of data collection and database finalization in late 2026. A manuscript reporting the primary findings is expected to be submitted for publication in April 2027.

## Discussion

This randomized active-comparator crossover trial is expected to clarify whether short-term pain reduction differs between 2-Hz and 100-Hz electroacupuncture in patients with postoperative musculoskeletal pain. These results will directly inform the optimal frequency selection and outcome assessment timing for future definitive efficacy trials. The paired physiological measurements are expected to provide preliminary information on whether short-term analgesic responses are accompanied by changes in photoplethysmography-derived PRV and radial pulse tonometry parameters.

The rationale for comparing 2-Hz and 100-Hz electroacupuncture is based on frequency-dependent analgesic mechanisms. Low-frequency electroacupuncture (2 Hz) is expected to preferentially activate β-endorphin and enkephalin pathways with descending serotonergic and noradrenergic inhibition, whereas high-frequency electroacupuncture (100 Hz) is expected to engage dynorphin-mediated spinal antinociception [20]. We hypothesize that these distinct pathways will contribute to observable differences in both subjective pain relief and objective physiological measures. This protocol extends prior postoperative electroacupuncture research by using an intraindividual crossover design, a conservative washout period, and concurrent patient-reported and physiological measures to characterize short-term frequency-dependent responses.

The strengths of this trial include its randomized crossover design, within-participant comparison of 2 active electroacupuncture frequencies, standardized bilateral ST36 to SP9 stimulation, prespecified short-term outcome time points, and concurrent physiological measurements. The frequency-masked procedure, separation of the outcome assessor from the treating practitioner whenever feasible, and blinded statistical analysis are intended to reduce bias related to subjective pain assessment.

Certain limitations should be considered. First, as an active-comparator trial lacking a sham or inactive control, this study is designed to compare frequency-dependent responses rather than evaluate the absolute efficacy of electroacupuncture or control for placebo effects. Second, although participants will not be informed of the assigned stimulation frequency, masking may be incomplete because sensory perceptions can differ between 2-Hz and 100-Hz stimulation. Third, this is a single-center study with a modest sample size, which limits generalizability and precludes meaningful subgroup analyses. Fourth, postoperative pain may change with the recovery phase; therefore, days since surgery will be recorded and considered in the analysis. Finally, PRV derived from photoplethysmography will be used as a surrogate for electrocardiogram-derived heart rate variability, and findings from PRV should be interpreted accordingly.

The findings will be used to estimate effect size and variability, refine outcome timing, and inform sample size calculations for a future definitive trial. Future studies should consider including sham, usual care, or no-additional-electroacupuncture control groups; assessor blinding where feasible; multicenter recruitment; and stratification by surgical procedure, pain phenotype, analgesic use, and postoperative recovery phase. The results of this trial will be disseminated through peer-reviewed publications and conference presentations.

## Data Availability

The data used for analysis in this study are available upon request from the corresponding author. These data are not publicly available because of privacy concerns.

## Abbreviations

AE: adverse event
CONSORT: Consolidated Standards of Reporting Trials
eCRF: electronic case report form
IRB: institutional review board
NRS: numerical rating scale
PRV: pulse rate variability
SPIRIT: Standard Protocol Items: Recommendations for Interventional Trials
